Building on the evidence in support of AAC models, this hybrid effectiveness-implementation trial will evaluate the impact of a proactive enrollment strategy that links smokers seeking LCS with a digital cessation intervention comprising a WEB program and integrated TXT alone and in combination with TTS counseling. Our trial is guided by the RE-AIM framework [70] which provides a systematic way to evaluate the impact of the implementation of public health interventions on five criteria: reach; efficacy/effectiveness; adoption; implementation; and maintenance. This study will focus on reach, effectiveness, and adoption. The primary outcome is biochemically confirmed smoking abstinence at 12 months. The specific aims are as follows: Aim 1 (Effectiveness): to evaluate the comparative effectiveness of WEB + TXT and WEB + TXT + TTS vs a usual care (UC) AAR control group. *Hypothesis 1a:* WEB + TXT + TTS yields higher quit rates than WEB + TXT and UC. *Hypothesis 1b:* WEB + TXT yields higher quit rates than UC; Aim 2 (Implementation): to examine whether proactive enrollment increases treatment use and whether treatment use mediates the relationship between treatment assignment and smoking outcome. *Hypothesis 2a:* Proactive enrollment in WEB + TXT will yield greater levels of treatment use than passive referral to the same interventions in UC. *Hypothesis 2b:* Increases in treatment use will mediate the relationship between treatment group and outcome; Aim 3 (Reach and Adoption): to examine the representativeness of the study sample relative to all smokers screened for LCS eligibility (reach) and the potential for intervention implementation (adoption) among LCS clinics.

Our trial is structured as a practical clinical trial [71] to answer key questions about implementation and effectiveness of direct relevance to decision-makers. The evaluation of interoperable, digital technologies to deliver a sustainable, scalable cessation intervention and to facilitate its integration within clinical practice will add to the growing knowledge base about the overall effectiveness of digital interventions and their role in the healthcare delivery system.

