### Power calculation

Positive (i.e. abnormal) LCS findings increase the odds of abstinence [6, 97–99]. Therefore, to be conservative in our sample size calculations, efficacy estimates for UC are based on data from patients in previous trials with negative screening results. Among patients with negative findings in the National Lung Screening Trial, one-year abstinence rates are in the range of 9.7% [100] to 12.6% [97]. In the Danish Lung Cancer Screening Trial [98], patients received < 5 min of counseling from a nurse and 30-day abstinence at one-year follow-up was 11.4% among patients with no significant LCS findings. Cox et al. [101] reported seven-day abstinence at one year of 13%. Brief counseling for smoking cessation (<3 min) yields six-month abstinence rates of 13.4% [43]. Therefore, we conservatively estimate that biochemically verified abstinence at 12 months for UC will be 10%.

Efficacy estimates for WEB + TXT are based on several converging lines of evidence: (1) two meta-analyses have reported statistically significant effects of interactive and individually tailored interventions compared to usual care or written self-help (relative risk [RR] = 1.48, 95% confidence interval [CI] = 1.11–2.78 [30]; RR = 2.10, 95% CI = 1.25–3.52 [33]; (2) a meta-analysis by Webb et al. [102] found that the use of TXT in Internet interventions had large effects on behavior change (d = 0.81, k = 4); (3) combined Internet and TXT interventions yielded six-month sustained abstinence of 17.1% in Borland et al. [103] and 12-month repeated point prevalence abstinence of 20% in Brendryen et al. [46]. Therefore, we conservatively estimate that biochemically verified abstinence at 12 months for WEB + TXT will be 16%.

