#### Aim 2 (Implementation) analyses

First, we will examine treatment uptake and engagement via self-reported treatment use (behavioral or pharmacologic) and automated tracking data from the BecomeAnEX WEB and TXT program at each follow-up interval. We will test whether proactive enrollment in treatment yields higher levels of treatment uptake and engagement than AAR UC using descriptive statistics. We hypothesize that overall utilization will be higher for participants proactively enrolled in WEB + TXT compared to participants provided passive referrals to the same interventions in UC. Next, we will examine whether treatment engagement mediates the treatment-outcome relationship. To assess whether treatment engagement is predictive of improved abstinence outcomes and whether treatment engagement mediates the treatment effect, we will perform a series of additional logistic regression analyses following the framework described by Baron and Kenny [107]. The Aim 2 analytic plan is depicted in Fig. 2.

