**Fig. 2 Fig2:**
[figure not shown]
Mediational model

Here, X is the exogenous variable (treatment), Z is the hypothesized mediator (treatment engagement), Y is the outcome (abstinence at month 12), a is the regression path between treatment and the mediator, b is the regression path between the mediator and the outcome, and c’ is the regression path between treatment and the outcome controlling for the effect of the mediator.

To test mediation hypotheses, we will use the approach described by MacKinnon and Dwyer for binary mediator and outcome variables [108]. We will establish mediation as follows: (1) logistic regression will assess whether the effect of treatment assignment on abstinence is statistically significant; (2) logistic regression will assess whether the effect of treatment assignment on treatment use is statistically significant; (3) multivariable logistic regression will determine whether treatment use is statistically associated with abstinence after adjustment for treatment assignment; and, (4) we will assess whether the effect of treatment assignment on outcome is significantly attenuated in magnitude relative to step 1.

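### The mediation rule for Aim 2 requires a significant total effect on abstinence, so a detectable path through treatment use goes undeclared when that total effect is modest

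*Protocol article*

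**What the plan says.** The specific aims in the Background state Hypothesis 2b: "Increases in treatment use will mediate the relationship between treatment group and outcome". Under Aim 2 (Implementation) analyses the article adopts a causal-steps approach: "we will perform a series of additional logistic regression analyses following the framework described by Baron and Kenny".

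The text below Fig. 2 labels the paths: a from treatment to use, b from use to abstinence, and c' from treatment to abstinence given use. It then gives the decision rule:

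- Step 1 (total effect): "We will establish mediation as follows: (1) logistic regression will assess whether the effect of treatment assignment on abstinence is statistically significant".
- Step 2 (path a): "2) logistic regression will assess whether the effect of treatment assignment on treatment use is statistically significant".
- Step 3 (path b): "multivariable logistic regression will determine whether treatment use is statistically associated with abstinence after adjustment for treatment assignment".
- Step 4 (attenuation): "we will assess whether the effect of treatment assignment on outcome is significantly attenuated in magnitude relative to step 1".

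The same text cites a published approach for binary mediators and outcomes. It specifies no stand-alone estimate or interval for the indirect effect, and it does not say that mediation can be concluded when step 1 is non-significant.

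**The concern.** The path named in Hypothesis 2b is absent if a = 0 or b = 0. The four-step rule concludes mediation only if the total effect c is significant as well, so it can also fail because c is too small to detect. The total effect is usually the least precise of these tests, because the effect of use is diluted by everyone whose use did not change with assignment.

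The mediation result is most informative when WEB + TXT vs UC comes out modest. The question then is whether proactive enrolment failed to raise use, or raised use that helped too few people. In that situation the rule is likely to withhold the conclusion even when paths a and b are both significant.

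A modest contrast is not far-fetched. The Power calculation section cites usual-care-like abstinence of 9.7% to 13.4% and then plans on 10% for UC. A UC rate nearer the top of that range narrows the contrast with 16%.

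**Working it through.** **Inputs from the article (Power calculation).** 550 per group; planned abstinence 10% (UC), 16% (WEB + TXT) and 24% (WEB + TXT + TTS); a cited upper rate of 12.6% from the National Lung Screening Trial. Missing outcomes count as smoking (Aim 1 analyses), so all 550 per arm enter.

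**Assumptions, not in the article.** Use 15% in UC and 60% in WEB + TXT; abstinence depends on use only (complete mediation); no use-abstinence confounding; each step tested two-sided at 0.05 in the hypothesised direction; step 4 tested with a product-of-coefficients z.

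**1. The plan's own figure.** For 10% vs 16% the mean is 0.13.
- SE under the null: √(2 × 0.13 × 0.87 / 550) = 0.0203.
- SE under the alternative: √((0.10 × 0.90 + 0.16 × 0.84) / 550) = 0.0202.
- z = (0.06 − 1.96 × 0.0203) / 0.0202 ≈ 1.00, so power is about 84%.

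The article states more than 85% for each pair. The small gap is not part of this point. This 84% is also the power of step 1 at the planned rates.

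**2. Step 1 alone at smaller contrasts.** The same formula gives 53% at 10% vs 14%. At 12.6% vs 16% the mean is 0.143, both SEs are about 0.0211, and z = (0.034 − 0.0414) / 0.0211 = −0.35, so power is about 36%.

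**3. Abstinence by use implied by complete mediation.** The user minus non-user difference is d = (t1 − t0) / (0.60 − 0.15), where t0 and t1 are the arm rates. The non-user rate is t0 − 0.15d.
- 10% vs 16%: d = 0.133; non-users 8.0%, users 21.3%.
- 10% vs 14%: d = 0.089; non-users 8.7%, users 17.6%.
- 12.6% vs 16%: d = 0.076; non-users 11.5%, users 19.0%.

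**4. Simulated power of the rule.** Two arms of 550, Wald tests from the logistic regressions.

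| UC vs WEB + TXT | Step 1 alone | Steps 2–4 (no step 1) | All four steps |
|---|---|---|---|
| 10% vs 16% | 84% | >99% | 84% |
| 10% vs 14% | 53% | 97% | 51% |
| 12.6% vs 16% | 36% | 86% | 31% |

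In each row the last column is close to the product of the other two (for example 0.36 × 0.86 = 0.31). The loss therefore comes from step 1. For WEB + TXT + TTS vs UC at 24% vs 10%, step 1 has over 99.9% power and there is essentially no loss.

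**5. Other assumed use rates.** With 10/50%, 20/60% and 10/70%, the loss from step 1 is about 15–17 points at 10% vs 16%, 34–48 at 10% vs 14%, and 33–62 at 12.6% vs 16%.

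**6. False conclusions without step 1.**
- No confounding and no effect of use: paths a and b are jointly significant in the same direction in about 2.5% of trials, and the product test rejects in 4.4–4.6%.
- Shared cause: suppose an unmeasured binary factor (50% prevalence) raises both use and abstinence, use itself has no effect, and base abstinence is 10% or 13%. False mediation without step 1 is then about 7–9% at an odds ratio of 2 on each link and about 20–27% at an odds ratio of 3. With step 1 it stays under 1%.

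**The case against.** **Step 1 does protect against something.** Since the unconfounded error rates are below 5%, a reader might infer that the total-effect condition adds no protection and can be dropped at no cost. The documents do not support that. Use is self-selected after randomisation, the Background describes patients whose interest in quitting varies, and coordinators enrol participants directly, so path a will probably be large. A rule built on a and b then rests mainly on the non-randomised association b, while step 1 is a randomised comparison on abstinence. The shared-cause simulation shows what is given up. This objection stands and shapes the fix. Step 1 is still not a remedy for confounding: once any total effect is significant, the same bias passes through steps 3 and 4.

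**The analysis is not switched off.** A reader might infer that the mediation work stops when step 1 fails. The text does not say so. It says the effect will be assessed, Aim 2 separately commits to examining uptake and whether engagement predicts abstinence, and the Statistical analyses section promises point estimates with 95% intervals throughout. What is withheld is the conclusion.

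**Hypothesis 2b may presuppose a total effect.** It speaks of mediating a relationship, so one can argue that a relationship must be shown first. That reading is possible, so the rule should not be called a contradiction of the hypothesis. Even so, a non-significant result at 550 per arm does not show that the relationship is absent.

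**Step 4 already addresses the indirect effect.** True. The fault is the added condition, not the absence of any such test.

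**Conclusion.** The point holds as a limited one. The opening words of the rule and the named framework make a significant total effect a condition for concluding mediation, and nothing in the article relaxes this. For UC vs WEB + TXT, about one detectable mediation in six is lost at the planned rates. The loss is about 46 points at 10% vs 14% and 55 points at 12.6% vs 16%. These sizes rest on assumed use rates, complete mediation, no confounding and a 0.05 level per step. The large losses need a total effect below the planned 6 points. The primary outcome, its tests and the sample size are unaffected. It is worth changing because a better rule is cheap to write, provided the confounding that step 1 partly guards against is dealt with directly.

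**What to change.** - Remove step 1 as a condition. For each contrast, report the indirect effect with a 95% bootstrap interval, together with the total and direct effects, whether or not the total effect is significant. Base the mediation conclusion on the indirect effect.
- Adjust the use-abstinence model for variables already listed under Baseline variables: readiness and confidence to quit, nicotine dependence, quitting history and demographics.
- Add a sensitivity analysis showing how strong an unmeasured shared cause of use and abstinence would have to be to remove the indirect effect.
- Where mediation is concluded with a non-significant total effect, say so in the same sentence.

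The cost is a rewording, a bootstrap, and an adjusted model using data the trial already collects. The downside is that the conclusion leans more on a non-randomised association. Unadjusted, the assumed shared cause gives false mediation in about 7–27% of trials, so the adjustment and sensitivity analysis must accompany the removal of step 1.

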#### Baseline variables

To characterize the sample and examine moderators of treatment effectiveness, the baseline assessment will assess: demographics (age, sex, ethnicity, race, marital status, education, number of household tobacco users); perceived vulnerability and worry about lung cancer (personal risk of developing cancer, their likelihood compared to other smokers, and their level of worry about getting lung cancer); current smoking and smoking history (smoking frequency and rate, lifetime and past 30-day use of other tobacco products and e-cigarettes); motivation to quit smoking will be measured with the Readiness Ladder [88, 89] and an item regarding confidence in quitting; quitting history, including past year quit methods; nicotine dependence will be measured with the Fagerström Test for Nicotine Dependence [90].

The following metrics will be extracted from the BOSS Registry for all patients that are determined eligible for LCS: age; education; race/ethnicity; body mass index; referral source; and smoking status. We will compare patients eligible for LCS to study participants on these characteristics to evaluate representativeness of the study sample.

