#### Process variables

Treatment utilization will be assessed via self-report at each follow-up and automated tracking metrics extracted from BecomeAnEX and the BOSS Registry. At each follow-up, participants will be asked about their use of any cessation methods. The following metrics will be extracted from BecomeAnEX: total time spent logged into the website; number of return visits; use of the static content and videos; use of interactive components/tools; number of replies to interactive text messages; unsubscribe rates; modal day of unsubscribe; number of days enrolled in TXT; and number of text messages received. The following metrics will be extracted from BOSS regarding completion of TTS counseling: number and duration of completed TTS counseling sessions; tobacco use status; confidence and importance for quitting or maintaining abstinence; medication use; cravings/urges and management strategies.

TTS intervention fidelity will be monitored throughout the study via review of digital audio recordings. Audio review will be conducted using a fidelity measure based on the Mayo Clinic treatment model including items adapted from the Motivational Interviewing Treatment Integrity Code [60].

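### The four-step test of Hypothesis 2b adjusts self-selected treatment use for arm alone, so a confounder of use and quitting can produce a finding of mediation when use has no effect

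*Protocol article*

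**What the plan says.** The Background states Hypothesis 2b: "Increases in treatment use will mediate the relationship between treatment group and outcome". Under Aim 2 (Implementation) analyses, "we will perform a series of additional logistic regression analyses following the framework described by Baron and Kenny". The text below Fig. 2 adds that "we will use the approach described by MacKinnon and Dwyer for binary mediator and outcome variables", and then sets out four steps by which mediation will be established:

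- Step 1: "logistic regression will assess whether the effect of treatment assignment on abstinence is statistically significant".
- Step 2 does the same for the effect of arm on treatment use.
- Step 3: "multivariable logistic regression will determine whether treatment use is statistically associated with abstinence after adjustment for treatment assignment".
- Step 4: "we will assess whether the effect of treatment assignment on outcome is significantly attenuated in magnitude relative to step 1".

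The mediator is behaviour after randomisation. Under Process variables, "Treatment utilization will be assessed via self-report at each follow-up and automated tracking metrics extracted from BecomeAnEX and the BOSS Registry".

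Likely common causes of use and quitting are measured at entry. Under Baseline variables, "motivation to quit smoking will be measured with the Readiness Ladder", together with confidence in quitting, the Fagerström score and smoking rate. The purposes given there for these variables are description and moderator analysis; control of confounding is not one of them.

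**The concern.** Randomisation protects the arm-to-use and arm-to-abstinence comparisons. It does not protect the use-to-abstinence path, because participants decide how much treatment to use. The section on LCS eligibility screening says that interest in quitting is not needed for referral, so motivation should vary widely. Within an arm, a more motivated or less dependent smoker is likely both to use more treatment and to quit more often. Adjusting for arm does not remove that association.

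Step 3 can then be significant for a reason unrelated to any effect of use. Because arm shifts use strongly, putting a confounded use term into the model also pulls the arm coefficient towards zero, which is what step 4 looks for. At stake is the mechanistic conclusion of Aim 2: that proactive enrolment works by raising treatment use.

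**Working it through.** **The plan's own figure first.** No power or error rate is stated for the mediation analysis. The nearest figure is the pairwise power in Power calculation, which governs step 1: 550 per arm, 10% v 16%, stated as above 85%.

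- Pooled SE = √(2 × 0.13 × 0.87 / 550) = 0.0203
- Unpooled SE = √((0.10 × 0.90 + 0.16 × 0.84) / 550) = 0.0202
- z = (0.06 − 1.96 × 0.0203) / 0.0202 ≈ 1.00, so power ≈ 84%

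That is within about one point of the stated figure. Under the design assumptions, step 1 is usually passed.

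**Inputs to the simulation.**

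- From the protocol: 550 per arm; abstinence 10% (UC), 16% (WEB + TXT) and 24% (WEB + TXT + TTS); the four steps.
- Assumed, because the documents give no value: use 20% in UC and 60% (or 40%) in the proactive arm; one standard-normal common cause U with log-odds γ per SD on both use and abstinence, γ from 0 to 1.0.

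**Model.** logit P(use) = α(arm) + γU and logit P(abstinent) = β(arm) + γU. There is no use term in the abstinence model, so the true effect of use is zero. Intercepts are set so that the marginal rates equal those above. Each step counts as met if significant at two-sided 0.05 in the hypothesised direction. Step 4 tests the change in the arm log-odds ratio with a standard error that allows for both models being fitted to the same data. There were 2,000 trials per row.

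**UC v WEB + TXT, use 20% v 60%:**

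| γ | Apparent OR for use | Apparent attenuation | Step 1 met | Step 4 met | All four met |
|---|---|---|---|---|---|
| 0 | 1.00 | 0% | 84.1% | 2.0% | 1.7% |
| 0.3 | 1.09 | 7% | 83.5% | 5.7% | 4.6% |
| 0.5 | 1.26 | 17% | 83.4% | 20.8% | 17.1% |
| 0.7 | 1.52 | 32% | 83.9% | 55.1% | 46.5% |
| 1.0 | 2.15 | 58% | 84.6% | 97.3% | 82.2% |

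Step 2 is met in every trial. The last column is close to the product of the two before it; for γ = 0.7, 0.839 × 0.551 = 0.462. The Monte Carlo standard error at 46.5% is √(0.465 × 0.535 / 2000) = 1.1 points. A separate run gave 1.7%, 4.0%, 17.0%, 47.8% and 81.4%.

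**Variations, for γ = 0.5, 0.7 and 1.0:**

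- Use 20% v 40%: 16.3%, 46.0%, 81.9%.
- UC v WEB + TXT + TTS (10% v 24%): 24.3%, 64.3%, 98.8%.
- Sobel test in place of step 4: 17.1%, 47.0%, 82.3%.

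**No arm effect (10% v 10%).** All four steps are met in 0.1% (γ = 0) to 2.5% (γ = 1.0) of trials, because step 1 closes the sequence.

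**Effect of baseline adjustment (all four met, γ = 0.5, 0.7 and 1.0):**

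- Adjusting for U itself: 1.8%, 2.1%, 2.3%.
- Baseline proxy of reliability 0.8: 3.3%, 5.2%, 11.0%.
- Baseline proxy of reliability 0.5: 6.7%, 16.6%, 45.7%.

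**The case against.** Four points on the other side carry weight.

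1. *Step 1 protects against false confirmation.* It does when the arm has no effect. When the arm has the planned effect it opens about 84% of the time and gives little protection.

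2. *An arm effect wholly outside treatment use is hard to construct here.* Both arms receive the medication booklet and the same brief counselling, UC is referred to the same website and text program, and Aim 2 counts behavioural and pharmacological use. This stands as a limit on size: zero effect through use is the extreme case. The confounded path itself does not depend on that case. If use has some real effect, motivation still distorts its estimate and the apparent share mediated.

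3. *The documents give no confounder strength.* Correct. At log-odds 0.3 the excess is small, so only the range can be reported.

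4. *An unseen analysis plan may add covariates.* Possible. The article does not say that arm is the only covariate, and its rule against covariate adjustment is confined to the primary analysis. But it presents these steps as how mediation will be established and names an adjustment for step 3, so the wording should be completed there.

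A reader might also infer three further faults, which the documents do not support.

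- *Comparing logistic coefficients across models creates spurious mediation.* Without confounding the rule is met in only 1.7% of trials. With use balanced across arms and a log-odds effect of use of 1.0 to 2.0, the change of scale moves the arm coefficient away from zero by about 3% to 10%, against step 4. The plan also cites a method for binary mediators and outcomes, so an unscaled comparison cannot be presumed.
- *Requiring a significant step 1 is an error.* It is conservative, and it fits a hypothesis about mediation of an arm-outcome relationship.
- *Use after quitting or relapse will be counted as a cause.* The article says that use is measured at each follow-up. It does not fix the mediator's window, and that detail is commonly left to the analysis plan.

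**Conclusion.** The point holds in a limited form. As written, step 3 leaves the use-abstinence path open to confounding, and the four steps can then confirm Hypothesis 2b when use has no effect. Two conditions are needed: a common cause of use and quitting, and an arm effect arising at least partly by routes other than measured use.

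In the extreme case of no effect through use, false confirmation runs from about 4–5% at confounder log-odds 0.3 per SD to about 82% at 1.0, with about 17% and 47% at 0.5 and 0.7; the reference without confounding is about 2%. The direction is secure. The size rests on assumed confounder strength and, less sensitively, on assumed use rates. This concerns an Aim 2 hypothesis only; the primary abstinence comparison is not affected.

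**What to change.** - In the outcome models of steps 1, 3 and 4, adjust for one common set of baseline covariates: site, readiness to quit, confidence, Fagerström score and smoking rate. Using the same set throughout keeps the step 4 comparison like with like.
- Add a sensitivity analysis for unmeasured confounding of use and abstinence. It is needed because baseline measures are imperfect proxies: in the simulation at log-odds 0.7, adjustment lowered false confirmation from 46.5% to 5.2% with reliability 0.8, but only to 16.6% with reliability 0.5.
- State that the result will be described as an association between use and abstinence unless it survives that sensitivity analysis.

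The cost is a few lines of plan text, modest extra programming and possibly a more cautious Aim 2 conclusion. All the covariates are already collected, and neither the sample size nor the primary analysis changes.

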**Discussion:**

The scalability and sustainability of a digital intervention may represent the most cost-effective and feasible approach for LCS programs to proactively engage large numbers of smokers in effective cessation treatment. We will also evaluate the impact and cost-effectiveness of adding proven clinical intervention provided by a TTS. We expect that a combined digital/clinical intervention will yield higher quit rates than digital alone, but that it may not be as cost-effective or feasible for LCS programs to implement. This study is innovative in its use of interoperable, digital technologies to deliver a sustainable, scalable, high-impact cessation intervention and to facilitate its integration within clinical practice. It will add to the growing knowledge base about the overall effectiveness of digital interventions and their role in the healthcare delivery system.

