### Statistical analyses

Unless otherwise specified, analyses use an ITT approach that analyzes individuals by treatment assignment. We will use descriptive statistics to summarize demographic data, tobacco use history, and other baseline characteristics. Summaries will be generated for the entire sample and by treatment arm. Given the randomized design, we will not assess for significant baseline treatment differences. With the exception of the stratification variable, no covariate adjustment will be included in the primary analysis. For all exploratory analyses, two-tailed *p* values will be reported with no adjustment for multiple comparisons. In all cases, findings will be reported using point estimates and corresponding 95% CIs. Model assumptions for each analysis will be validated and transformations or non-parametric methods will be utilized as appropriate.

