We will compare total and incremental costs to implement each intervention from a payer perspective. Implementation costs of the two interventions will be estimated using average market values for salaries of the additional staff needed to perform the TTS counseling and market costs of the digital intervention. If a treatment effect is observed, we will assess cost per quit and incremental cost per quit. Cost-effectiveness of the two proposed study interventions compared to usual care will be estimated by employing a Markov Model [109, 110]. Hypothetical cohorts representing the U.S. population will be simulated through long-term screening. Disease progression will be modeled with transition probabilities of developing lung cancer. Model parameters not directly measured in the proposed trial will be supplemented with data from the literature, including the publicly available Lung Cancer Policy Model of the Cancer Intervention and Surveillance Modeling Network [111–113]. Model complexity specific to our modeling environment will be determined by available data for the model parameters. A simplistic design not incorporating smoking status (current vs smoker) will be used as the model basis. Smoking status will be incorporated if identified data prove to make this feasible. If not feasible, the simplistic model design will serve as a crucial starting point for further analyses in the future. Sensitivity analyses will be conducted to determine the impact of changes in key model inputs.

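### Within-trial cost per quit and incremental cost per quit are made conditional on an undefined 'observed' treatment effect, so the only stated analysis that prices the TTS increment per quit may be dropped

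*Protocol article*

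**What the plan says.** The relevant text is the cost paragraph that closes the Aim 2 (Implementation) analyses, after Fig. 2. It has three layers.

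- Costs, without condition: "We will compare total and incremental costs to implement each intervention from a payer perspective".
- Within-trial cost-effectiveness, with a condition: "If a treatment effect is observed, we will assess cost per quit and incremental cost per quit". The paragraph does not say whether 'observed' means statistically significant, significant for the pair concerned, significant for any pair, or simply a favourable estimate.
- A model, without that condition: "Cost-effectiveness of the two proposed study interventions compared to usual care will be estimated by employing a Markov Model". Its starting structure is limited: "A simplistic design not incorporating smoking status (current vs smoker) will be used as the model basis". The next step is itself conditional: "Smoking status will be incorporated if identified data prove to make this feasible".

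The Discussion part of the Abstract undertakes, with no condition, to evaluate the cost-effectiveness of adding TTS counseling, and gives the expectation: "We expect that a combined digital/clinical intervention will yield higher quit rates than digital alone, but that it may not be as cost-effective". The opening paragraph under Statistical analyses sets a general reporting rule: "In all cases, findings will be reported using point estimates and corresponding 95% CIs".

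**The concern.** Whether TTS counseling is worth its added cost over the digital programme is a question about cost and effect together, for WEB + TXT + TTS against WEB + TXT. The protocol fixes a rule under which the effect side may be left out of that comparison. A non-significant difference is still an estimate with an interval, and that interval may include gains that would justify the cost. Dropping the ratio discards this information when the decision is closest.

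The condition also has no rationale for cost per quit within an arm, which is that arm's cost divided by its quits and needs no between-arm effect.

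If the condition is a significance test, there is a second consequence. The ratios that are reported rest on effect estimates selected for being large, so incremental cost per quit tends to look too low when the true effect is modest.

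**Working it through.** **Inputs.** From Power calculation: 550 per group; planned 12-month abstinence 10% (UC: "we conservatively estimate that biochemically verified abstinence at 12 months for UC will be 10" percent), 16% (WEB + TXT) and 24% (WEB + TXT + TTS); two-tailed tests; step-down cut-offs 0.0167, 0.025 and 0.05. The same section cites 21.5% as the lowest quit rate for combined Internet and TTS counseling (30-day abstinence, so only a guide to the 12-month endpoint). The 20% TTS rate and the 10/13%, 10/14/18% and 10/16/20% patterns are assumptions.

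**Formula.** For rates p1 and p2 with mean p̄ and difference d:
- SE0 = √[2p̄(1−p̄)/550]
- SE1 = √{[p1(1−p1)+p2(1−p2)]/550}
- power ≈ Φ[(d − 1.96·SE0)/SE1]; miss rate = 1 − power

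**The plan's own figure.** The plan states at least 99% power overall and more than 85% for each pair. Recomputed: overall 99.99%; at alpha 0.05, 84.2% (10% vs 16%), 91.4% (16% vs 24%) and above 99.9% (10% vs 24%). The lowest is within a point of the stated figure, so it reproduces closely enough.

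**Reading A: the condition is a significant test for the pair concerned (alpha 0.05).**

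| Comparison | d | SE0 | SE1 | (d − 1.96·SE0)/SE1 | Miss rate |
|---|---|---|---|---|---|
| 16% vs 24% (plan) | 0.080 | 0.0241 | 0.0240 | 1.36 | 9% |
| 16% vs 21.5% | 0.055 | 0.0235 | 0.0235 | 0.38 | 35% |
| 16% vs 20% (assumed) | 0.040 | 0.0232 | 0.0231 | −0.23 | 59% |
| 10% vs 16% (plan) | 0.060 | 0.0203 | 0.0202 | 1.00 | 16% |

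Simulating the full step-down rule at the planned rates gives nearly the same misses: about 16% for WEB + TXT vs UC and 9% for TTS vs WEB + TXT. UC vs TTS is almost always detected, so the later cut-offs usually apply. About 24% of trials miss at least one of the three comparisons.

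**Reading B: one significant comparison among the three arms is enough.** Simulated chance that none is significant under the step-down rule: under 0.01% at 10/16/24%, about 0.8% at 10/16/20%, about 6% at 10/14/18%.

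**Selection when the condition is met under Reading A.** At a fixed incremental cost, the reported ratio relative to the truth is (true d)/(estimated d). Its mean among significant results (alpha 0.05, 400,000 simulated trials per scenario):
- true 16% to 20%: mean significant estimate 6.2 points; ratio about 0.67 of its true value
- true 16% to 19%: about 0.53
- planned 10% to 16%: 0.97
- planned 16% to 24%: 1.01

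**What a missed effect would hide.** Suppose the trial observed 10% vs 13%. The difference is 3.0 points, 95% CI −0.8 to 6.8, p = 0.12. Under Reading A no ratio is produced. Yet the point estimate implies 1/0.030 ≈ 33 times the incremental cost per participant for each extra quit, and the upper limit implies 1/0.068 ≈ 15 times. The interval also contains the planned 6-point gain for WEB + TXT over UC.

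**Can the Markov model stand in?** Two of its stated features limit it. Its comparisons are of each intervention with usual care, so TTS against WEB + TXT is not among them. And a base design without smoking status may not carry the trial's quit difference at all.

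**The case against.** A reader might infer that the plan treats a missed effect as equal effectiveness, compares the arms on cost alone, and lets the cheaper arm win by default. The document supports none of these. It contains no decision rule of that kind. Its general reporting rule means quit-rate estimates and 95% CIs will appear beside the costs whatever the p-value, and a Markov cost-effectiveness analysis is planned without the condition. Nor is the bias general: at the planned effects it is negligible.

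Other points on that side also carry weight. The protocol writes 'statistically significant' elsewhere when it means that, and here refers to one treatment effect rather than to pairs. Reading B is therefore open, and under it the 9% to 59% miss rates do not apply. Cost is in none of the numbered hypotheses. The choice of bootstrap or acceptability curve is detail that an article normally leaves to the full protocol or analysis plan.

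What survives is narrower. The condition is a rule the article states, not a detail it omits. A reader could divide published costs by published differences, but would not get the joint uncertainty. The Markov model does not cover the TTS increment as described. If 'observed' means only a favourable estimate, there is no p-value threshold, but the ratio is still reported selectively.

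**Conclusion.** The point holds in limited form. The within-trial cost per quit and incremental cost per quit depend on an undefined condition, which sits badly with the unconditional undertaking in the Abstract to evaluate the cost-effectiveness of adding TTS. The size depends on what the condition means. As a pairwise significance test, it removes the TTS-versus-digital ratio in about 9% of trials at the planned rates, rising to 35% and 59% at the two smaller TTS effects examined; for WEB + TXT vs UC it is about 16% at the planned rates. As any one significant comparison, it almost never bites at the planned rates. The favourable bias matters only under the pairwise reading and for effects well below plan.

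These figures assume 550 analysed per arm (missing counted as smoking) and unadjusted two-proportion tests in place of the site-adjusted logistic model. The matter is worth correcting, but it concerns a secondary economic analysis; the primary outcome, its test and the sample size are untouched.

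**What to change.** Delete the opening condition from the cost-per-quit sentence. Report cost per quit for each arm, and incremental cost and incremental quits for all three pairwise comparisons, whatever the significance of the abstinence tests. Give joint uncertainty for cost and effect; one suitable form is a bootstrap interval for incremental net benefit over a range of values per quit. Net benefit stays stable when the effect is near zero, whereas the ratio does not, and that instability is the one sensible motive for a condition. Also confirm whether the Markov model will take in the estimated quit difference and its uncertainty.

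The cost is a change of wording and some analysis of data already being collected, with no new patients or visits. The downside is that imprecise incremental results will be reported when the effect is small, and they should be labelled as such.
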